## Abstract

**Background:**

Discharged against medical advice (DAMA) is a risk factor that often leads to adverse outcomes and hospital readmissions in neonatal units. A few studies have shown that spiritual/faith-based interventions (FBIs) tend to have a lower incidence of DAMA compared with public hospitals. Perhaps, a holistic approach to patient care that addresses the spiritual needs, the soul and the body component of a being in this setting may account for the observed lower incidence of DAMA. Limited randomized control trials (RCTs) exist on FBIs with regard to DAMA in the published literature. This study seeks to compare the effectiveness of FBI, social support, religiosity, and types of FBI on neonatal DAMA against standard of care in tertiary hospitals in Nigeria.

**Methods:**

This RCT will be conducted in two public tertiary teaching hospitals in two of the six geopolitical zones in Nigeria. The sociodemographic and clinical details of all patients admitted to the neonatal wards during the study period will be documented. Study participants will be selected through a multistage sampling technique. Subjects will be randomized and allocated to treatment and control arms having the established baseline measure of social support and religiosity. Ethical approval was obtained from the State Research Ethics Review Committee. A written informed consent will be obtained from the parents/caregivers prior to patient enrolment. The study will be conducted in line with the Declaration of Hesinki 2000. Appropriate statistical tools will be used for data collection and analysis.

**Discussion:**

The outcome of this analysis will give insights into the effectiveness of FBI on DAMA. It will also predict the effect of the mediators of parents/caregivers' religiosity, spirituality, forms of FBI, the religious sect of parents/caregivers, and social support on the rate of DAMA on neonatal admission in tertiary hospitals in Nigeria. This could help Public Health Institutions and Governments make decisions about the determinants of neonatal DAMA and how to mitigate such outcomes. It is hoped that the evidence from this study may guide policy formulation and guidelines on enhancing hospital retention of sick neonates until they are fit for discharge.

**Trial Registration:**

This study was registered at the Pan Africa Clinical Trial Registry (PACTR202102670906630).

## Background and Rationale

Approximately 130 million babies are born annually, about 4 million of these newborns in low- and middle-income countries (LMICs) do not survive beyond the neonatal period (1). More worrisome is the increasing contribution of childhood mortality from the neonatal death. This narrative is not different in Nigeria where neonatal mortality represents one of the highest in the world, only behind India (2).

The reasons for this trend are multifactorial. They vary from ignorance, harsh healthcare workers altitude to caregivers/parents, poverty, the lack of access to good healthcare, the need for spiritual support at a very trying time, and discharged against medical advice (DAMA) (3–7). It is, therefore, important that those who get to a health service be treated holistically, providing physical, psychological, and spiritual support to enable them complete treatment until when discharge is recommended by the treating clinicians (3–5).

Discharged against medical advice occurs when an in-patient decides to leave the hospital before discharge is recommended by the treating clinicians or physicians. DAMA poses serious clinical, ethical, and legal challenges to the individual physician as well as to the hospital (1, 6–9). The DAMA prevalence has been shown to vary depending on geographical areas and the study population. The rate of DAMA compares inversely with the socioeconomic status: a relatively lower rate was observed at a hospital serving primarily middle- and upper-class populations, whereas a higher rate was observed at a hospital serving disadvantaged urban areas (9–13). The pediatric age group, and especially the newborns are at a greatest risk for DAMA in Nigeria from the published literature (9–11).

Discharged against medical advice has been shown to increase the risk of adverse outcomes ranging from medical complications requiring readmission to death (6, 8). Associated outcomes also include higher morbidity, increased mortality, longer hospital stays, and higher costs of treatment when readmitted (10, 11).

More challenging with DAMA is the ethical issues in neonates as they have the least autonomy to participate in their health decision. The parents/caregivers entrusted with the right of decision-making often fail this vulnerable population. The very sick babies with a risk for residual long-term outcomes, higher risk for mortality, and foreseeable future of being a burden are often thought of dispensing with by the parents/caregivers, and hence there is a request for DAMA. This poses a great challenge to the managing physician on maintaining a balance between the parents/caregivers autonomy against the fiduciary role of the physician (4, 6, 8).

A few observational studies have shown lower incidences of DAMA in faith-based hospitals where spiritual leaders actively participate in patient care (14–20). A holistic approach to patients' care that addresses the spiritual needs, the soul, and the body component of a being in this setting may account for the observed lower incidence of DAMA. However, it may not be sufficient to explain the lower incidence of DAMA with just the involvement of the spiritual leader in care, the literature has suggested that a number of variables can interact to influence decision-making. In this instance, perceived social support of parents/caregivers of newborns as well as their levels of religiosity may significantly influence the decision to engage in DAMA (20–22). Limited randomized control trial (RCT) studies on the effectiveness of faith-based intervention (FBI) are available in the published literature.

This protocol provides a workflow for an open label randomized clinical trial to evaluate the effectiveness of spiritual/FBI intervention on hospital retention of neonates compared with standard of care in tertiary hospitals. It also includes secondary outcomes such as patients' clinical outcome, parents/caregivers' satisfaction with intervention, and their desire to see the intervention established as routine care for newborns in a public tertiary hospital.

## Objectives

### General Objective

The general objective is to determine the effectiveness of religion intervention rates of DAMA in neonates.

### Specific Objectives

To determine:

a comparison of the effectiveness of religion intervention with standard of care on newborn rates of DAMA.the association in case of between clinical and sociodemographic characteristic of patients on the rates of DAMA.the delineation of the reasons for DAMA among neonates in Nigeria.a model for a prediction of the rates of DAMA in neonates using explanatory variables (reasons) for DAMA.the effect of parents/caregivers religiosity, spirituality, types of FBI, the religious sect of parents/caregivers, and social support on the outcomes of DAMA or hospital retention till discharge.

### Trial Design

#### Intervention Assignment

This will be an open label, parallel RCT.

Simple randomization using a randomization table created by a computer software program would be used for randomization.

Allocation sequence would be concealed in sealed opaque envelopes.

## Methods: Participants, Interventions, and Outcomes

### Study Setting

This study is a multicenter study involving two public tertiary hospitals located in two of the six geopolitical zones/regions in Nigeria (23, 24). The selected tertiary hospital includes University College Hospital Ibadan and The Federal Medical Center Katsina, Katsina state as shown in Figure 2.

### Eligibility Criteria

#### Inclusion Criteria

All newborns admitted into selected public hospitals whose parents/caregivers gave their consent to participate in this study.

#### Exclusion Criteria

Babies whose parents/caregivers fail to give consent for this study.Babies were taken into custody by institutions such as motherless home or by government agencies for legal reasons.

### Who Will Take Informed Consent?

Prior to recruitment, the research would be explained to parents/caregivers by the investigator who will obtain a written informed consent. Parents/caregivers will be informed of their freedom to refuse to take part in this study without any negative consequences to them or their wards in the course of treatment.

### Additional Consent Provisions for the Collection and Use of Participant Data and Biological Specimens

Additional consent would be obtained for data availability for secondary analysis and for ancillary studies in the future.

### Interventions

#### Explanation for the Choice of Comparators

The comparator will provide standard of care for all babies admitted to a newborn unit. The active treatment of control arm is in line with basic principles of medical ethics for RCT.

#### Intervention Description

There will be two arms of this study; one arm (the experimental arm) will receive a FBI. The FBI will involve religious counseling encouraging the caregivers/parents to stay in the hospital until their baby is medically discharged. This will also involve offering prayers and reading of holy books for the babies recovery. Each participants will have two to three sessions of the FBI with each session lasting 20–30 min.

The control arm will be exposed to standard of care observed for all babies admitted to a newborn unit.

### Criteria for Discontinuing or Modifying Allocated Interventions

Participant who also wishes to exit study after due counseling.

### Strategies to Improve Adherence to Interventions

Prior to recruitment, parents/caregivers of study participants will be educated on the study in order to gain their cooperation.

### Relevant Concomitant Care Permitted or Prohibited During the Trial

Both the experimental and control group will have access to the same treatment except for the intervention in the experimental arm.

### Provisions for Post-trial Care

The outcome of measure is a one-time off measure and would not require a follow-up.

### Outcomes

#### The Primary Outcome

The primary outcome of this study is the retention rate of sick newborns with the FBI in public tertiary hospitals in Nigeria compared with the standard of care.

#### Secondary Outcomes

The secondary outcomes are the reasons and determinants of DAMA among neonates in tertiary hospitals in Nigeria.

The effect of parents/caregivers religiosity, spirituality, types of FBI, the sect of parents/caregivers, and social support on the outcomes of DAMA or hospital retention in neonatal admission.

Patients' clinical outcome.Parents/caregivers' satisfaction with intervention and their desire to see the intervention established as routine care for newborns in a public tertiary hospital.

### Participant Timeline

#### Sample Size

The details of participant timeline is shown in Table 1. The sample size required for this study was determined using the Raosoft sample size calculator (http://www.raosoft.com/samplesize.html) for single proportion with estimated 50% prevalence of DAMA. A sample size of 359 has 80% power to detect the prevalence of cerebral malaria at an alpha level of probability 0.05.

**Table 1 T1:** Participant timeline (25).

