### Statistical Methods for Primary and Secondary Outcomes

Data from this study will be analyzed in GraphPad Prism 9 (GraphPad Software, San Diego, CA, USA). The appropriate descriptive statistics will be used to present the sociodemographic characteristics of study participants. The comparison of categorical outcomes between the arms will be analyzed using the Chi-squared or Fisher's exact tests, as appropriate, and presented as risk differences, risk ratios, or odds ratios and 95% CIs. The values of *p* < 0.05 will be considered statistically significant for all analyses.

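### The sample size of 359 comes from a single-proportion calculation, so the stated 80% power has no basis for the two-arm comparison of DAMA or retention

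*Protocol article*

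**What the plan says.** The Sample Size section of the protocol article says that the number was "determined using the Raosoft sample size calculator", "for single proportion with estimated 50% prevalence of DAMA". The next sentence gives the result: "A sample size of 359 has 80% power to detect the prevalence of cerebral malaria at an alpha level of probability 0.05". Those two sentences are the whole justification in the article.

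The trial itself is comparative. The first specific objective is "a comparison of the effectiveness of religion intervention with standard of care on newborn rates of DAMA". The Primary Outcome section names the "retention rate of sick newborns with the FBI in public tertiary hospitals in Nigeria compared with the standard of care". The statistical methods section says: "The comparison of categorical outcomes between the arms will be analyzed using the Chi-squared", with Fisher's exact test as the alternative and risk differences, risk ratios or odds ratios reported with 95% confidence intervals. Trial Design, Sampling Technique and Allocation describe two parallel arms under simple randomisation.

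**The concern.** The method and the question do not match. A single-proportion calculation answers how closely one prevalence can be estimated. The trial asks whether DAMA differs between arms, and power for that needs a rate in each arm, or one rate and a difference. The article gives one rate only.

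The power sentence is also about a condition that appears nowhere else in the document. It looks like text carried over from another study. Correcting the name alone would leave power to detect a prevalence of DAMA, which is still not power for a between-arm difference.

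At stake is the only statement of what the trial can detect. A reader will take from it 80% power for the faith-based intervention against standard of care, and nothing in the article supports that.

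**Working it through.** **Inputs in the Sample Size section.** n = 359; power 80%; alpha 0.05, sidedness not given; one proportion, 50%. Not given anywhere in the article: margin of error, population size, second-arm rate or target difference, allocation ratio, and whether 359 is the total or per arm.

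**Step 1: can 359 be reproduced?** The usual single-proportion formula is n = z²p(1−p)/m². With z = 1.96, p = 0.5 and an assumed margin m = 0.05, n = 0.9604/0.0025 = 384.2, or 385 rounded up. That is not 359. Two unstated inputs would produce 359:
- a finite population of about 5,470 at the same margin: n = N × 0.9604/((N−1) × 0.0025 + 0.9604) = 5,253.4/14.63 = 359;
- no finite-population correction and a margin of 1.96 × √(0.25/359) = 5.17 points.

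Both are back-solved. The article states neither, so 359 cannot be rebuilt from what it gives. That this was a precision calculation is itself an inference from the words single proportion and prevalence.

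**Step 2: where could the 80% come from?** The formula above contains no power term. Read instead as a one-sample test against 50%, 359 has 80% power for a shift of about 7.4 points (two-sided) or 6.5 points (one-sided). No such alternative is stated, and it would not be the trial's comparison.

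**Step 3: what 359 gives for two arms.** Assumptions: two-sided alpha 0.05, 1:1 allocation, control DAMA p₁ = 50%, and retention taken as the complement of DAMA so that either gives the same power. With n per arm and p̄ = (p₁+p₂)/2:

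power = Φ{[(p₁−p₂) − 1.96·√(2p̄(1−p̄)/n)] / √([p₁(1−p₁)+p₂(1−p₂)]/n)}

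Example, 50% against 40%:
- 359 in total, n = 179.5: (0.100 − 1.96 × 0.05251)/0.05225 = −0.056, so power is 47.8%.
- 359 per arm: (0.100 − 1.96 × 0.03713)/0.03694 = 0.737, so power is 76.9%.

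| Fall in DAMA from 50% to | Power, 359 in total | Power, 359 per arm |
|---|---|---|
| 45% | 15.6% | 26.8% |
| 40% | 47.8% | 76.9% |
| 35% | 82.3% | 98.3% |
| 30% | 97.4% | about 100% |
| Rate detectable with 80% power | 35.4% (14.6 points) | 39.6% (10.4 points) |

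**Step 4: lower control rates.** These rates are my assumptions; the article does not give them. Same formula, 80% power:

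| Control DAMA | Detectable rate, 359 in total | Detectable rate, 359 per arm |
|---|---|---|
| 30% | 17.5% | 20.9% |
| 20% | 9.5% | 12.3% |
| 10% | 2.8% | 4.6% |

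I give no row for 5%. For 359 in total the approximation returns 0.3%, which is about 0.5 expected events in the treated arm (179 × 0.003). Exact enumeration at 180/179 for 5% against 0.3% gives about 88% power by chi-squared and 77% by Fisher's test, so 0.3% is not a sound 80% threshold.

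**The case against.** The strongest reply is that the cerebral malaria phrase is an obvious slip, since the sentence before it says DAMA, and that 359 may serve the trial well enough. The first half is fair as far as the name goes, but changing the name supplies neither a second rate nor a difference. The second half also stands: 359 in total reaches 80% power for a fall of about 15 points from 50%, and 359 per arm does so for about 10 points. The point is therefore not that the trial is too small. Adequacy cannot be judged without a target difference.

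A second reply is that the detail may sit in a fuller protocol or an analysis plan. That would answer a charge of omission. Here the article states a basis for its sample size, and the basis does not support the power it claims.

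A third is that any single figure for the two-arm power rests on assumptions. That is right, and it is why both readings of 359 are shown.

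Some stronger conclusions are tempting but not supported:
- A reader might infer that 80% power holds only if DAMA is near 50%. Step 4 shows otherwise: with 359 in total the detectable absolute fall shrinks from 14.6 points at 50% to 12.5, 10.5 and 7.2 points at 30%, 20% and 10%. The relative reduction required is what grows.
- A reader might infer that a null result could not be interpreted. The planned 95% confidence intervals would still show which differences are excluded.
- A reader might infer that the ethics committee was told of 80% power. The article records approval only, not what the committee read.

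**Conclusion.** The point holds as a mismatch of method. The Sample Size section describes a one-proportion calculation and attaches 80% power to something the trial does not measure; with the condition's name corrected, it is still not power for the primary comparison. It is not a proven arithmetic error, because the inputs needed to check 359 are missing.

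Power for falls of 5 to 20 points from 50% runs from about 16% to 97% if 359 is the total, and from about 27% to nearly 100% if it is per arm. The 80% level is met only for falls of about 14.6 or 10.4 points respectively. These figures rest on two-sided alpha 0.05, 1:1 allocation and control DAMA of 50%; only the alpha level and the 50% prevalence come from the article, and the article does not assign that prevalence to the control arm. The power statement must be corrected, since it is the sole justification offered for the number randomised.

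**What to change.** In the Sample Size section:

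1. Delete the sentence that claims 80% power for cerebral malaria.
2. Keep the statement that 359 came from a single-proportion calculation at 50%, and add the margin of error and any population size used. Readers should not be led to think that 359 came from a two-arm calculation.
3. State whether 359 is the total or per arm, the allocation ratio and the sidedness of alpha.
4. State the two-arm power as a consequence of 359, not as a target chosen beforehand. If 359 is the total: 80% power for a fall from 50% to about 35%, 48% for a fall to 40% and 16% for a fall to 45%. If it is per arm: 80% for a fall to about 39.6%, 77% for a fall to 40% and 27% for a fall to 45%.
5. Add detectable differences for lower control rates, labelled as assumptions, with exact power where expected events are few.

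The cost is protocol wording. An unconditional 80% gives way to a conditional and less favourable statement. The correction does not itself change enrolment; it also gives no assurance that 359 is enough for whatever difference the investigators consider important.

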	**STUDY PERIOD**							
	**Enrolment**	**Allocation**	**Post-allocation**					**Close-out**
**Timepoint**	** *-t_1_* **	**0**	** *12hs* **			** *72hrs* **		** *t_x_* **
**Enrolment:**								
Eligibility screen	X							
Informed consent	X							
*Administration of research screening tools*	X							
*Clinical history and examination*	X					X		
Allocation		X						
**Interventions:**								
*[Intervention A]*			X  X				
*[Intervention B]*							
**Assessments:**								
*[List outcome variables]*								X

#### Recruitment

The details of patients' recruitment are shown in the study participant flow chart in Figure 1.

**Figure 1 F1:**
[figure not shown]
Study participant flow chart.

**Figure 2 F2:**
[figure not shown]
Map of the study centers in Nigeria.

*Invitation*: the caregivers/parents of eligible patients will be verbally invited during their hospital admission.

*Eligibility*: subjects will be assessed based on the eligibility criteria enumerated earlier.

*Enrolment*: eligible subjects will be enrolled into this study after giving a written informed consent.

*Informed consent*: parents and caregivers will give a written informed consent during enrolment. This will be signed by Principal Investigator, the parent/caregiver, and a witness. A copy of informed consent will be retained by the parent, while a copy will be kept in the patient's file.

#### Sampling Technique

*In stage I*, the list of tertiary hospitals in Nigeria will form the sample frame for this study. A random number will be allocated to each center. Two institutions will be randomly selected from this list.

*In Stage II*, an allocation sequence for the two arms will be generated using simple randomization from GraphPad Prism version 9. In the selected hospitals, consecutive neonates whose parents/caregivers give an informed consent would be allocated to one of the two arms based on the allocation sequence.

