### Assignment of Interventions: Allocation

#### Sequence Generation

A random number will be generated using simple randomization from GraphPad Prism version 9 for consecutive patients being enrolled for this study.

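### Neonates are allocated one by one although the intervention and the DAMA decision sit with the parents, so co-enrolled twins can be split between arms and the effect diluted

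*Protocol article*

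**What the plan says.** The unit of allocation is fixed as the baby in two places. Sampling Technique states that "consecutive neonates whose parents/caregivers give an informed consent would be allocated to one of the two arms based on the allocation sequence", and Sequence Generation states "A random number will be generated using simple randomization from GraphPad Prism version 9 for consecutive patients being enrolled for this study".

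Multiples are eligible. The Inclusion Criteria admit "All newborns admitted into selected public hospitals whose parents/caregivers gave their consent to participate in this study". Apart from refusal of consent, the only exclusion is "Babies were taken into custody by institutions such as motherless home or by government agencies for legal reasons". No rule covers siblings.

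The intervention and the decision both sit with the parents. Intervention Description: "The FBI will involve religious counseling encouraging the caregivers/parents to stay in the hospital until their baby is medically discharged", to which prayers and readings for the baby's recovery are added. Background and Rationale, on who decides: "The parents/caregivers entrusted with the right of decision-making often fail this vulnerable population".

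The intended contrast is set out under Relevant Concomitant Care: "Both the experimental and control group will have access to the same treatment except for the intervention in the experimental arm". The arms are compared by chi-squared or Fisher's exact test (Statistical Methods).

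**The concern.** If twins are enrolled and each takes the next entry in the sequence, one may fall in the FBI arm and the other in standard care. The same parents are then counselled to stay for one baby and count as unexposed for the other. The contrast promised under Relevant Concomitant Care cannot hold for that family. If the counselling works, the control twin is also more likely to stay, and the measured difference between arms is smaller than the true one.

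The stake is a bias towards no effect and some lost power. It cannot produce a false positive. Exposure of a split family cannot be undone at analysis, so the rule is best set before enrolment.

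**Working it through.** **The plan's own figure.** The total is 359, from a single-proportion calculation at 50%. With an assumed 5% margin and 95% confidence, n = 1.96² × 0.25 / 0.05² = 384.1, so 385. A finite-population correction gives 377 for a population of 20,000 and 370 for 10,000. The figure 359 appears only for an unstated population of about 5,250 to 5,470. That is a separate matter; here 359 is simply the number randomised, about 179.5 per arm.

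**Assumed inputs.** The documents do not give the allocation ratio (1:1 assumed), the share s of enrolled babies with an enrolled co-twin (5, 10 and 20% tried), the within-family correlation ρ (0.5 to 1.0 tried) or a target effect (15 points used for illustration).

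**Step 1: splitting.** Two independent 1:1 allocations differ with probability 2 × 0.5 × 0.5 = 0.50. For triplets the chance that not all three share an arm is 1 − 2 × 0.5³ = 0.75.

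**Step 2: contaminated controls.** Pairs = 359 × s / 2; split pairs = half of these; contaminated share f = split pairs / 179.5 = s / 2.

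**Step 3: dilution.** If the exposed co-twin gets the full effect, the observed effect is the true effect × (1 − f).

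**Step 4: power.** With 179.5 per arm, 80% power is reached for 50% against about 35.4%, a difference of 14.58 points. With contamination the control rate becomes 50 − 14.58 × f.

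| s | Pairs | Split pairs | f | 15 points becomes | Control rate, step 4 | Power |
|---|---|---|---|---|---|---|
| 5% | 9.0 | 4.5 | 2.5% | 14.6 | 49.6% | 78.0% |
| 10% | 18.0 | 9.0 | 5% | 14.25 | 49.3% | 75.9% |
| 20% | 35.9 | 18.0 | 10% | 13.5 | 48.5% | 71.4% |

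**Step 5: type I error.** Code the arm as +1 or −1. A pair's correlation enters the variance of the difference multiplied by the product of the two arm codes. With independent 1:1 allocation that product averages zero: unsplit pairs widen the variance, split pairs narrow it, and they offset. A simulation (20,000 runs per setting, no effect, 50% event rate, ρ = 1) gave these rejection rates for the ordinary two-proportion test:

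| s | Neonate allocated (as planned) | Family allocated, analysed as independent |
|---|---|---|
| 5% | 5.1% | 5.3% |
| 10% | 4.7% | 6.1% |
| 20% | 5.1% | 7.1% |

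The simulation error is about √(0.05 × 0.95 / 20,000) = 0.15 percentage points.

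**The case against.** **Tempting but unsupported: the chi-squared standard error is too small.** A reader might infer this because twins share a family and the test treats them as independent. Step 5 shows that it does not follow for this plan, even with perfectly correlated twins. Inflation, and a design effect of 1.05 to 1.20, arise only if siblings are allocated together and then analysed as independent.

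**Tempting but unsupported: the damage is beyond repair.** The exposure itself cannot be reversed. But splitting is decided by randomisation alone, so a sensitivity analysis without split pairs is possible if siblings can be identified in the data.

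**Full sharing is an upper bound.** Nothing in the article says that one decision always covers all siblings. Background and Rationale links requests to leave with how ill the individual baby is, so co-twins may differ, and part of the FBI is prayer for a particular baby. This stands: the dilution figures are the worst case for each twin share.

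**The effect is small and rests on assumed inputs.** This also stands. At a 5 to 10% twin share the loss is about 2 to 4 points of power; only the 20% end is noticeable.

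**The full protocol or SAP may deal with multiples.** A sibling rule may exist there, and its absence from an article alone would be no fault. But the article is not silent on the unit: it states twice that each consecutive baby or patient is allocated. That is a stated choice, and an analysis plan cannot undo a split.

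**Conclusion.** The point holds as a contamination problem. Allocation is by neonate, while the counselling and the decision are the parents', and multiples are not excluded. With 1:1 simple randomisation about half of co-enrolled twin pairs would be split. For twin shares of 5 to 20%, 2.5 to 10% of controls would have exposed parents. Both the twin share and the full carry-over of effect to the co-twin are assumptions. The bias is towards the null and modest at the lower twin shares. The planned test remains valid for type I error under the present allocation. It is a cheap improvement of minor to moderate severity.

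**What to change.** **Allocation (Sampling Technique, Sequence Generation).** Make the mother or family the unit: one envelope per mother, with co-enrolled siblings taking the same arm.

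**Analysis (Statistical Methods).** Keep retention of each neonate as the primary outcome, and compare arms with family-clustered standard errors or GEE. The two changes belong together, because the ordinary test becomes anti-conservative once siblings share an arm. Confirm that the named software fits such models, or name one that does. A family outcome such as any sibling leaving is not advised: it would change the stated primary outcome and would depend on the number of siblings.

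**Cost.** One sentence on allocation, one on analysis, and a smaller effective sample size. The design effect is about 1 + s × ρ. For ρ of 0.5 to 1.0, matching the precision of 359 independent babies needs 368 to 377 at a 5% twin share, 377 to 395 at 10%, and 395 to 431 at 20%.

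If recruitment stays at 359, power is approximately Φ(2.802 / √(1 + sρ) − 1.960), where 2.802 = 1.960 + 0.842 is the value for 80%. This gives 79.0 to 78.1% at s = 5%, 78.1 to 76.1% at 10% and 76.1 to 72.5% at 20%. These are only slightly above the contaminated figures when ρ is near 1. The main gain is therefore an undiluted estimate and a clean contrast between arms, not recovered power.

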### Assignment of Interventions: Blinding

#### Who Will Be Blinded

This is an open label trial. The intervention and comparator will not be concealed. Both the investigator and the subject will be aware of what intervention they would receive.

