#### Methods in Analysis to Handle Protocol Nonadherence and Any Statistical Methods to Handle Missing Data

The result of this study will be analyzed per protocol. Missing data will be accounted and the proportion with a desirable outcome will be presented.

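### Table 1 leaves an interval between allocation and the first FBI session in which the arm is known; with the per-protocol set undefined, departures in it either dilute the comparison or bias it towards the FBI

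*Protocol article*

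**What the plan says.** All references are to the protocol article.

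- **Allocation.** Stage II of Sampling Technique: "consecutive neonates whose parents/caregivers give an informed consent would be allocated to one of the two arms based on the allocation sequence". No waiting time is stated.
- **Timeline.** Table 1 has consent, screening tools and a clinical history in the enrolment column (before time 0), allocation at 0, then post-allocation columns at 12 and 72 hours. The row for "Intervention A" has its first mark in the 12-hour column and none at 0. The row is broken in the text available, so the place of the second mark is uncertain.
- **FBI.** Intervention Description: "Each participants will have two to three sessions of the FBI with each session lasting 20–30 min". No time is given for the first session.
- **Masking.** Who Will Be Blinded: "Both the investigator and the subject will be aware of what intervention they would receive".
- **Endpoint.** The section that defines it reads: "The primary outcome of this study is the retention rate of sick newborns with the FBI in public tertiary hospitals in Nigeria compared with the" (the sentence then names the control arm). No start time is given for counting departures.
- **Analysis set.** The section on nonadherence and missing data: "The result of this study will be analyzed per protocol". The term is not defined.

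**The concern.** Between allocation and the first session both arms receive the same care, and family and investigator know the arm. A departure in that interval cannot have been prevented by counselling, prayer or reading. If the arms do differ there, the cause is a reaction to learning the allocation, yet the difference would be credited to the FBI.

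The protocol does not say how such departures enter the primary comparison. An FBI family that leaves before any session has plainly not received the planned sessions, so a per-protocol rule could remove it. A control family that leaves in the same hours has no session to miss and would stay. Depending on how the rule is read, the trial either loses power or shows a benefit that is not real. Nothing in the document requires allocation before the first session is due, because consent and the baseline tools already come earlier.

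**Working it through.** **The plan's own figure.** Sample Size uses a calculation "for single proportion with estimated 50% prevalence of DAMA" and reports 359. With p = 0.5, 95% confidence and an assumed 5-point margin, n = 1.96² × 0.25 / 0.05² = 384.1, so 385. A result of 359 needs an unstated input, such as a 5.17-point margin or a finite population of about 5,470. The figure is therefore not reproduced from the stated inputs. That is a separate matter; 359 is used here only as the number allocated.

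**Inputs**
- Control DAMA 50%: Sample Size.
- 180 FBI v 179 control: 359 split 1:1; the ratio is assumed.
- Risk ratio RR for DAMA once the FBI has started: 0.70, or 1.0 for no effect. Assumed.
- f, the share of control-arm DAMA that falls between allocation and the first session: not in the document; shown from 0 to 30%.
- Knowing the arm changes nothing during the interval. Assumed.
- Two-sided 5% test of two proportions. Power = Φ[(|p1 − p2| − 1.96·√(p̄(1 − p̄)(1/n1 + 1/n2))) / √(p1(1 − p1)/n1 + p2(1 − p2)/n2)].

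**Case A: every allocated baby counts from time 0.** FBI risk = 0.5f + 0.5(1 − f) × 0.70. At f = 20%: 0.10 + 0.28 = 0.38, a difference of 12.0 points. Power = Φ[(0.120 − 0.1027)/0.0520] = Φ(0.333) = 63%.

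**Case B: FBI families who left before any session are dropped, controls are all kept.** FBI risk = 0.5(1 − f)·RR / (1 − 0.5f), against 0.50. With RR = 1 and f = 20%: 0.40/0.90 = 0.444, a false difference of 5.6 points. With RR = 0.70: 0.28/0.90 = 0.311, an apparent 18.9 points.

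**Case C: 359 allocated when the first session is due.** Control risk = 0.5(1 − f)/(1 − 0.5f); FBI risk = 0.70 of that. At f = 20%: 0.444 v 0.311.

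| f | A: difference (points) | A: power | B, no effect: false difference (points) | B, RR 0.70: difference (points) | C: power |
|---|---|---|---|---|---|
| 0% | 15.0 | 82.3% | 0 | 15.0 | 82.3% |
| 5% | 14.25 | 78.1% | 1.3 | 15.9 | 80.5% |
| 10% | 13.5 | 73.5% | 2.6 | 16.8 | 78.6% |
| 20% | 12.0 | 63.0% | 5.6 | 18.9 | 74.3% |
| 30% | 10.5 | 51.6% | 8.8 | 21.2 | 69.1% |

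In case B with no effect, the FBI arm keeps 180(1 − 0.5f) = 171, 162 and 153 babies at f = 10%, 20% and 30%. The chance of a significant result in favour of the FBI is then about 7%, 17% and 36%, where a two-sided 5% test should give 2.5%.

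**The case against.** **The direction of the harm.** A reader might infer that the plan as written counts the early departures and so dilutes the effect. The document does not support that. It gives no start for counting and plans a per-protocol analysis, under which the error could run the other way. Dilution follows only if all allocated babies are analysed. Even then it costs power and does not bias the estimate: the effect of offering the FBI, with its real delay, is a legitimate target. This objection stands, and for that reason neither direction is asserted here.

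**Allocation at the moment of consent.** This too is a tempting inference. Stage II gives no timing, and Table 1 separates enrolment from allocation. The point rests only on the interval from allocation to the first FBI mark.

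**The 12 hours.** The column could mean at 12 hours, by 12 hours, or a nominal first window. The table is broken as read and still carries template labels, and Figure 1 is not shown. The length of the interval is therefore uncertain. What remains is that no FBI mark stands at time 0.

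**Size and remedy.** The document gives neither f nor the risk ratio, and if f is small the gain is small. Later allocation also changes the population, and families still know their arm afterwards. All of this is true and limits the weight of the point, but none of it justifies leaving early departures without a stated handling.

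**Conclusion.** The point holds in conditional form. Table 1 shows an interval after allocation without FBI, the arm is known during it, and the protocol does not say how departures in it count.

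- If all allocated babies count, power falls from 82% to about 74%, 63% and 52% at f = 10%, 20% and 30%.
- If untreated FBI families are dropped and control families kept, the comparison is biased towards the FBI by 2.6, 5.6 and 8.8 points when there is no effect. This is the more serious outcome.

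These sizes rest on the protocol's 50% DAMA rate and on assumed values of f, the risk ratio and a 1:1 split. At f = 5%, later allocation raises power by only about 2 points (78.1% to 80.5%). The change is worth making because it is cheap and removes both problems, not because the loss is known to be large. Confidence is moderate, given the damaged table and the unknown f.

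**What to change.** Leave the FBI schedule as it is and change the following.

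1. **Stage II and Table 1.** Complete consent and baseline tools in the enrolment column, as now. Open the next sealed envelope when the first FBI session is due, by the same timing rule whichever arm is drawn, for families still in hospital. Make that moment time 0.
2. **Primary outcome.** Count DAMA from that time 0. Report departures between consent and allocation as a separate, unrandomised count.
3. **Nonadherence section.** State that the primary comparison includes all allocated babies in their allocated arm, whether or not a session took place. A per-protocol analysis can be kept as secondary, with its set defined for both arms. This step is needed even if the allocation time is not moved: it removes the one-sided exclusion, though not the loss of power.

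**Cost.** Some amended sentences, a moved mark in Table 1, and a check at envelope opening that the family is still present. The result then applies to families still in hospital when the FBI can start. To allocate 359, about 359/(1 − 0.5f) families must consent: 378 at f = 10% (about 5% more) and 399 at f = 20%. Awareness of the arm after allocation remains, as in any open-label trial.
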